1. SUMMARY OF THE RESEARCH

SPONSOR: CHU Amiens-Picardie PRINCIPAL INVESTIGATOR: [name], Clinical Fellow in Anesthesiology

TITLE: Evaluation of plasma concentrations of intravenous lidocaine and epidural ropivacaine when used in combination in major abdominal surgeries.

ACRONYM: LARA

BACKGROUND/CONTEXT: Major abdominal surgeries cause intense pain in both the intraoperative and postoperative periods. Management of this pain relies on epidural analgesia on one hand and intravenous lidocaine on the other. These two techniques are often used together. However, currently no study has evaluated the safety of this combination in major abdominal surgeries.

OBJECTIVES: The primary objective of this study is to evaluate the plasma concentrations of lidocaine and ropivacaine during the combination of an epidural anesthesia and intravenous lidocaine in a major abdominal surgery. The secondary objective is to investigate the undesirable side effects related to local anesthetics when combining epidural anesthesia with intravenous lidocaine during a major abdominal surgery (central nervous system effects: seizures, dizziness, convulsions, paresthesia, tongue numbness, hyperacusis, tinnitus, visual disturbances, dysarthria, muscle contractions, tremors; hypoesthesia; cardiac disorders: bradycardia, tachycardia, conduction disturbances possibly progressing to cardiac arrest). STUDY DESIGN: Before general anesthesia, patients undergoing major abdominal surgery via laparotomy will have a thoracic epidural catheter placed; however, no injection through the catheter will occur during the surgery. During surgery, patients will receive an intravenous bolus of lidocaine at 1.5 mg/kg (SFAR recommendations), followed by a continuous IV infusion of lidocaine at 2 mg/kg/h (SFAR recommendations), which will be stopped 30 minutes before the end of surgery (at the time of surgical closure). The epidural ropivacaine infusion will be started at the same time the lidocaine infusion is stopped, using ropivacaine 1 mg/mL with an initial minimum bolus of 5 mL, then maintained at a minimum rate of 5 mg/h via the epidural catheter for up to 24 hours postoperatively. The rest of the anesthetic protocol is at the discretion of the anesthesiologist in charge of the patient. As part of the study, blood samples will be taken to measure lidocaine plasma levels: 30 minutes after the induction bolus, at the time the continuous lidocaine infusion is stopped, and 2 hours after the start of the epidural ropivacaine infusion. Blood samples to measure ropivacaine plasma levels will also be taken 2 hours after the start of the epidural and 24 hours after the start of the epidural.

INCLUSION CRITERIA:

Patient undergoing major abdominal surgery with laparotomy

Age ≥ 18 years

Written informed consent obtained

Affiliated to a social security system (health insurance)

EXCLUSION CRITERIA:

Major abdominal surgery via laparoscopic approach

Contraindication to thoracic epidural placement (e.g. coagulation disorders, localized or systemic infection, shock or uncorrected hypovolemia, respiratory failure if block level > T7, severe aortic or mitral stenosis, obstructive cardiomyopathy, severe uncompensated heart failure)

Allergy to local anesthetics; Contraindication to IV lidocaine (acute porphyria, unpaced atrioventricular conduction disorders, severe heart failure, severe liver failure, uncontrolled epilepsy, treatment with Class I antiarrhythmics)

Contraindication to ropivacaine (allergy to local anesthetics, acute porphyria)

Major hepatectomy with vascular clamping

Patient refusal to participate

Minor (age < 18)

Patient under guardianship/curatorship or deprived of liberty

Pregnant, parturient, or breastfeeding women

Cognitive impairment precluding giving informed consent

STUDY TREATMENT/PROCEDURE: Induction with IV lidocaine 1.5 mg/kg followed by continuous infusion at 2 mg/kg/h (per SFAR guidelines), stopped at surgical closure. Immediately at discontinuation, initiation of thoracic epidural analgesia with ropivacaine, infused for 24h at a minimum of 5 mg/h after an initial minimum bolus of 5 mg via the epidural catheter. As part of the study, blood samples will be taken for lidocaine levels 30 minutes after the induction bolus, at the end of the continuous infusion, and 2 hours after starting the epidural ropivacaine infusion. Blood samples for ropivacaine levels will be taken 2 hours after starting the epidural and 24 hours after starting the epidural.

ENDPOINTS: The primary endpoint is the plasma concentration of ropivacaine and lidocaine falling outside the safe range at the various time points of management. For lidocaine, the safe plasma range is 1.4 to 6 µg/mL; neurotoxicity appears from 15 µg/mL and cardiotoxicity from 21 µg/mL. For ropivacaine, the usual maximum safe venous concentration is around 2.2 µg/mL. The secondary endpoint is the occurrence of clinical systemic toxicity of local anesthetics within 48 hours postoperatively, defined by any of the following events: central nervous system disturbances (seizures, dizziness, paresthesia, tongue numbness, hyperacusis, tinnitus, visual disturbances, dysarthria, muscle twitching, tremors, hypoesthesia) or cardiac disturbances (bradycardia, tachycardia, conduction disorder potentially progressing to cardiac arrest). This composite endpoint will be counted if at least one of the above events is present.

SAMPLE SIZE: 50 patients

NUMBER OF CENTERS: Single-center (CHU Amiens-Picardie)

STUDY DURATION:

Inclusion period: 12 months

Participation duration for each patient: 48 hours

Total study duration: 12 months

STATISTICAL ANALYSIS: We expect a low percentage of patients with ropivacaine or lidocaine levels outside the safe range. Assuming this percentage is about 10%, enrolling 50 patients would allow us to estimate this percentage with a confidence interval no wider than 16% (±8% precision). In any case, the percentage can be estimated with a precision no worse than ±14% (the worst precision corresponds to an incidence around 50%). EXPECTED

OUTCOMES: Demonstrating the safety of the lidocaine + epidural ropivacaine combination in laparotomy will support standardizing this practice. It will affirm and provide evidence that combining intravenous lidocaine with epidural analgesia using ropivacaine in major open abdominal surgery is safe, thereby encouraging uniform adoption of this analgesic strategy.

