3.1.2. On Reference Treatments/Strategies/Procedures and Those Under Study

Epidural anesthesia (EPA) is the gold standard for managing laparotomy pain. However, it induces sympathetic blockade and can cause hypotension, which may be dangerous for the patient and lead to intra- or postoperative organ dysfunction. Therefore, the infusion of local anesthetics through the epidural catheter is typically started only after the high-risk surgical stages are over – in practice, at the time of surgical closure. Intravenous lidocaine has multiple effects: anti-arrhythmic, anesthetic, analgesic, anti-inflammatory, antithrombotic, bronchodilatory, neuroprotective, and even antimicrobial properties. IV lidocaine infusion does not cause vasoplegia, whereas epidural anesthesia blocks sympathetic nerves and can reduce vascular resistance. The clinical analgesic efficacy of IV lidocaine has been confirmed by a 2018 meta-analysis. It is administered at the start of surgery (during induction) and continued intraoperatively until closure, at which point it is stopped. IV lidocaine via infusion pump is thus proposed as an alternative to epidural analgesia when the latter is contraindicated or if epidural placement fails. Depending on the chosen analgesic technique, there is a period not covered by local anesthetics: for lidocaine, this gap is at closure and immediate postoperative; for epidural, it is almost the entire intraoperative period until closure. This is why practitioners at our university hospital combine these two techniques. We know anecdotally from discussions with colleagues that this combined approach is also used in other hospitals, but no study has been conducted on the subject. However, there is a theoretical risk of local anesthetic toxicity with this combination, which dissuades some clinicians from using both techniques despite the potential significant benefit for patients. The combination of two local anesthetics is feasible only if we consider the kinetics of their plasma concentrations with each technique. Lidocaine is administered IV, whereas ropivacaine is administered into the epidural space. The systemic absorption of ropivacaine infused epidurally has been studied in several works, which showed plasma concentrations very far from toxic thresholds. This finding is reassuring for its concomitant use with IV lidocaine. However, we must consider whether there is any pharmacodynamic potentiation between these two drugs. Before attempting to demonstrate any clinical advantage of this combination for patient care, it is imperative to first ensure that combining them does not increase their toxicity. To date, although this combination is in widespread use, no study has been carried out to demonstrate its safety. Our study aims to show that toxic plasma thresholds are not reached when these two techniques are combined. We will also monitor for clinical signs of local anesthetic toxicity (central nervous system effects: seizures, dizziness, paresthesia, tongue numbness, hyperacusis, tinnitus, visual disturbances, dysarthria, muscle contractions, tremors; hypoesthesia; cardiac effects: bradycardia, tachycardia, conduction disturbance potentially progressing to cardiac arrest) when they are used together.

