5.2. Secondary Endpoints

The secondary endpoint is the occurrence (yes/no) of adverse events related to the use of local anesthetics, defined as any of the following:

Central nervous system symptoms: seizures, dizziness, loss of consciousness (“attacks”), paresthesia, numbness of the tongue, hyperacusis, tinnitus, visual disturbances, dysarthria, muscle contractions, tremors. Cardiac symptoms: bradycardia, tachycardia, conduction disorder possibly progressing to cardiac arrest. (If at least one of the above events occurs, it will count toward the endpoint.)

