10.6. Follow-up Visits

Follow-up begins once anesthesia induction is done and the lidocaine bolus has been administered. Clinically, this involves continuously monitoring and checking for any occurrence of local anesthetic adverse effects (cardiac and/or neurotoxicity) via physical exam and patient monitors (continuous ECG, BIS, invasive or non-invasive blood pressure, etc.) throughout the surgery and up to 24 hours postoperatively, whether the patient is in a standard ward or in ICU. We will also perform plasma measurements of lidocaine and ropivacaine at specific perioperative times: three lidocaine levels in total – the first 30 minutes after the induction bolus, one at the time the infusion is stopped (surgical closure), and the last one 2 hours after the epidural ropivacaine bolus; and two ropivacaine levels – the first 2 hours after the epidural bolus (at the same time as the last lidocaine level) and the second at 24 hours after epidural initiation.

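### The secondary toxicity composite has two different component lists, no working rule for attributing a sign to local anaesthetic, and follow-up windows that do not agree

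*Protocol*

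**What the plan says.** The Summary (section 1, Endpoints) sets the name and the window: "The secondary endpoint is the occurrence of clinical systemic toxicity of local anesthetics within 48 hours postoperatively". Its list ends with "visual disturbances, dysarthria, muscle twitching, tremors, hypoesthesia) or cardiac disturbances (bradycardia, tachycardia, conduction disorder potentially progressing to cardiac arrest", and its counting rule is "This composite endpoint will be counted if at least one of the above events is present".

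Section 5.2 defines the endpoint as "occurrence (yes/no) of adverse events related to the use of local anesthetics, defined as any of the following". Its CNS list includes loss of consciousness, glossed as attacks, and ends with "dysarthria, muscle contractions, tremors. Cardiac symptoms: bradycardia, tachycardia, conduction disorder possibly progressing to cardiac arrest". Again one item is enough. Section 5.2 states no time window.

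Section 4.2 (the objective) names both hypoesthesia and loss of consciousness, and speaks of signs that may be attributable to the combination. The Abstract also refers to attributable events and gives arrhythmias as an example. Section 12.2 analyses the percentage of patients with a toxic event, without saying which list applies.

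On follow-up, section 10.6 describes checking for local-anaesthetic effects by examination and monitors "throughout the surgery and up to 24 hours postoperatively". Section 6.1 follows patients for 48 hours, section 10.1 gives 48 hours of participation, the table in 10.2 ticks adverse event monitoring at every visit from Visit 1 to Visit 5, and 10.7 places Visit 5 on postoperative Day 2.

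**The concern.** When any one item makes a patient a case, each item on the list matters. Two lists that differ by one item in each direction can give two different rates from the same data, and the protocol does not say which list governs.

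The listed signs are also not specific to local-anaesthetic toxicity. Bradycardia and tachycardia carry no cause or degree. Hypoesthesia, in the Summary list, is not limited to areas outside the epidural block. There is no comparator arm (10.4), and the rest of the anaesthetic and analgesic regimen is discretionary (9.1), so a background rate can be neither subtracted nor assumed constant.

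Section 3.2 hopes to show absence of cumulative cardiac or neurological toxicity, and the Summary intends the result to support standardising the practice. If unrelated signs are counted, the combination may look harmful when it is not. If they are discounted informally after plasma levels are known, it may look safer than it is.

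**Working it through.** The protocol states no figure for this endpoint; the precision figures in 12.1 concern the primary proportion. The check is therefore a comparison of text, followed by an illustration.

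**1. The definitions side by side**

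| | Summary, Endpoints | Section 5.2 | Section 4.2 (objective) |
|---|---|---|---|
| Hypoesthesia | yes | no | yes |
| Loss of consciousness | no | yes (glossed as attacks) | yes (same gloss) |
| Muscle item | twitching | contractions | contractions |
| Window | 48 h postoperatively | none | none |
| Any single item counts | yes | yes | no counting rule |

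The operative conflict is between the Summary and 5.2, because 4.2 only says what will be looked for. A patient whose only sign is hypoesthesia is a case under the Summary and not under 5.2. A patient whose only sign is loss of consciousness is the reverse. Each such patient moves the rate by 1/50 = 2 percentage points.

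**2. Attribution**

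The Summary calls the composite systemic toxicity but counts the presence of a sign. Section 5.2 says related, then defines relatedness by the list itself. Section 11.3 asks the investigator to assess severity; it names no causality step. Attribution is thus intended but is not part of the rule that produces the count.

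**3. Time**

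Section 10.6 stops at 24 h; the Summary, 6.1, 10.2 and 10.7 run to 48 h or Day 2. How signs are to be detected between 24 h and Visit 5 is not stated. Read literally, a postoperative window also leaves out the intraoperative lidocaine infusion, although 10.2 (Visits 1 and 2) and 10.6 monitor it.

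**4. Illustration of the inflation (rates assumed)**

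Let t be the true toxicity rate and b the rate of listed signs from other causes, taken as independent. The composite rate is q = 1 − (1 − t)(1 − b). With t = 0, q = b. For n = 50, with exact (Clopper-Pearson) 95% intervals:

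| Assumed b | Expected cases (50 × b) | 95% CI at that count |
|---|---|---|
| 0% | 0 | 0 to 7.1% |
| 10% | 5 | 3.3 to 21.8% |
| 20% | 10 | 10.0 to 33.7% |
| 30% | 15 | 17.9 to 44.6% |
| 50% | 25 | 35.5 to 64.5% |

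With t = 1% and b = 5%, q = 1 − 0.99 × 0.95 = 5.95%, and the share of counted patients with true toxicity is 0.01/0.0595 = 17%. With t = 1% and b = 50%, q = 1 − 0.99 × 0.50 = 50.5%, and the share is 0.01/0.505 = 2%.

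**The case against.** The strongest reply is that relatedness is already in the text: 5.2 says related, 4.2 and the Abstract say attributable, and 6.1 refers to events related to local anaesthetics. Section 11.1 separates adverse events from related adverse effects, and 11.5 lists serious events judged related. Heart-rate cut-offs and reporting by component may properly sit in a statistical analysis plan that is not at hand. This stands as evidence of intent, and the absence of cut-offs is not held against the protocol. But nothing ties relatedness to the count, and an analysis plan should not have to choose between two protocol definitions.

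Three stronger readings are tempting and are not supported:

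- A reader might infer that nobody looks for toxicity after 24 h. Sections 6.1, 10.1, 10.2 and 10.7 provide follow-up to 48 h and an adverse event check on Day 2. Section 14.2 names postoperative clinical notes as source documents and 11.3 has non-serious events recorded in the CRF. What stands is the mismatch with 10.6 and the unstated method of detection after 24 h.
- A reader might infer that loss of consciousness makes every anaesthetised patient a case. Sections 4.2 and 5.2 gloss the item as attacks, which points to a seizure-like event and not to anaesthesia.
- A reader might infer that hypoesthesia would flag nearly every patient. The item is absent from 5.2, the Summary places it among CNS disturbances, and the documents give no frequency.

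Section 3.1.2 says of the epidural that "it induces sympathetic blockade and can cause hypotension". This shows that the epidural has circulatory effects of its own. It does not document how often bradycardia or tachycardia occurs, and hypotension is not in the composite.

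Finally, over-counting works against the result the sponsor hopes for, and attribution by unblinded investigators could push the rate down. That stands, and it shapes the fix.

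**Conclusion.** The concern holds in three limited parts. First, the Summary and 5.2 define different composites: one component differs in each direction, and the window is stated only in the Summary. This is certain from the text. Second, both count any listed sign without an attribution rule, so in a single-arm study unrelated heart-rate changes, and under the Summary list block-related hypoesthesia, would count as toxicity. The direction follows from the rule as written. The size does not: 5 to 25 of 50 patients rests on an assumed 10% to 50% background, zero true toxicity and no figure from the documents. It would be wrong to state as fact that the rate will mainly reflect the epidural or ordinary perioperative changes. Third, 10.6 does not agree with the other follow-up statements, and the Summary's window read literally omits the intraoperative period that the schedule monitors.

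This should be corrected before analysis. It affects the secondary endpoint only.

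**What to change.** - Use one component list, with the same terms, in the Summary, 4.2 and 5.2, and refer to it in 12.2.
- State one window with a start and an end, say whether the intraoperative period is included, and reconcile 10.6 with it, including how signs are sought after 24 h.
- If hypoesthesia is kept, exclude it within the segments blocked by the epidural.
- Have the investigator record, for each listed event, whether it is attributed to local anaesthetic, before the plasma results are seen.
- Report the attributed count and the any-cause count side by side, each with its 95% interval, and CNS and cardiac components separately.

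The cost is endpoint wording and one attribution field in the e-CRF, with no added visits or samples and no change in treatment. The downside is that attribution by open-label investigators is a judgement that could lower the reported rate. The any-cause count must therefore be reported beside it.

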2. ABSTRACT

Title: Evaluation of plasma concentrations of intravenous lidocaine and epidural ropivacaine when used in combination in major abdominal surgery. CHU Amiens-Picardie is the sponsor of this research. This research will be conducted with the support of [name of pharmaceutical company] / [source of funding (e.g., PHRC, internal grant, etc.)].

Background: Major abdominal surgery by laparotomy often requires effective analgesia. Thoracic epidural analgesia (TEA) is the gold standard for postoperative pain management in this setting and can be combined with intravenous lidocaine or used as an alternative when TEA is contraindicated, in order to reduce perioperative opioid use (which can cause side effects such as ileus or nausea/vomiting and delay enhanced recovery). Intravenous lidocaine and TEA share several properties (anti-hyperalgesic, anti-inflammatory, pro-kinetic for the intestines, anti-tumoral effects, etc.), suggesting an additive effect of their combination, which has not yet been studied.

Purpose: To demonstrate that thoracic epidural analgesia combined with intravenous lidocaine is safe and does not lead to adverse events during major abdominal surgeries.

Primary Outcome: Repeated measurements of plasma lidocaine and ropivacaine levels in the perioperative period.

Secondary Outcomes: Occurrence of adverse events attributable to local anesthetics – signs of neurotoxicity (e.g., tremors, seizures) and/or cardiotoxicity (e.g., conduction disturbances, arrhythmias, or the rare event of cardiopulmonary arrest).

Study Design: Lidocaine will be administered as an IV bolus during anesthetic induction and infused continuously until surgical closure (stopped ~30 minutes before the end). At the time of stopping lidocaine, ropivacaine will be injected through the thoracic epidural catheter and then infused for 24h. The occurrence of adverse events will be monitored through clinical examination and by measuring plasma lidocaine and ropivacaine levels during the perioperative period.

Eligibility Criteria:

Inclusion: Major abdominal surgery via laparotomy.

Exclusion: Laparoscopic approach, any contraindication to TEA, contraindication to ropivacaine or IV lidocaine.

Interventions: Blood samples for lidocaine level at 30 min before end of surgery, at end of infusion, and 2h after start of epidural ropivacaine; blood samples for lidocaine and ropivacaine levels 2h after start of epidural; and blood sample for ropivacaine level 24h after start of epidural infusion.

Number of subjects: 50 patients.

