
3.2. Research Hypotheses and Expected Results

Our hypothesis is that combining continuous IV lidocaine infusion with epidural anesthesia during management of a major abdominal surgery does not increase the plasma concentrations of local anesthetics beyond toxic thresholds. Through repeated blood sampling, we hope to show that plasma levels of the local anesthetics remain well below toxic values. Furthermore, by observing an absence of adverse events related to local anesthetic use (central nervous system effects – which are rare – such as seizures, dizziness, loss of consciousness, paresthesia, tongue numbness, hyperacusis, tinnitus, visual disturbances, dysarthria, muscle tremors; hypoesthesia; and cardiac effects such as bradycardia, tachycardia, conduction disturbances up to cardiac arrest), we hope to demonstrate no cumulative cardiac or neurological toxicity when both are used together.

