3.5. Expected Outcomes

Demonstrating the safety of this combination will initially allow us to standardize our practices. Combining IV lidocaine analgesia with epidural anesthesia appears very promising for managing patients undergoing major abdominal surgery, as this combination can modulate pain via different pathways. Currently, no study has shown the superiority of this combination over other analgesic techniques. Proving that no additional adverse effects occur when these two techniques are combined will allow those comparative studies to be performed and help identify the best therapeutic strategy for patients. This could optimize patients’ postoperative recovery.

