6. STUDY DESIGN

6.1. Study Schematic

This is a prospective, descriptive, single-center study. Patients undergoing major abdominal surgery via open laparotomy are included. The epidural catheter is placed at the beginning of the procedure, before induction of general anesthesia. An IV lidocaine bolus of 1.5 mg/kg is given at induction, then continued via infusion pump at 2 mg/kg/h. If the patient is obese (BMI > 30), the dosage will be adjusted based on ideal body weight as a precaution, although there are no specific guidelines on this point. The lidocaine infusion is stopped approximately 30 minutes before the end of surgery. At that same time, the epidural is “activated,” meaning an initial bolus of at least 5 mL of ropivacaine 1 mg/mL is given through the epidural, followed by a continuous infusion starting at a minimum rate of 5 mg/h. This rate will then be adjusted according to the patient’s pain in the recovery room. The total amount of ropivacaine administered will be recorded. Blood samples will be taken for lidocaine level 30 minutes after the bolus, at the end of the infusion, and 2 hours after the start of the epidural ropivacaine infusion. Blood samples for ropivacaine level will be taken 2 hours after the start of the epidural and 24 hours after the start of the epidural. Blood draws will be done through the arterial catheter placed for surgery. In the majority of cases, this catheter is maintained for 24h (patients are admitted postoperatively to a continuous care or intensive care unit). If the arterial line is removed earlier, the 24h ropivacaine sample will be obtained by venous puncture by the ward nurse or investigator. Each blood draw requires 6 mL of blood. The remainder of the anesthetic and analgesic protocol (besides the lidocaine and epidural as described) is left to the discretion of the anesthesiologist in charge of the patient. Patients will be followed for 48 hours postoperatively. Any adverse events related to local anesthetics will be monitored (clinically and with appropriate monitoring such as continuous ECG, etc.).

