10.4. Randomization

There is no randomization in this study (it is a single-arm descriptive study).

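### The protocol promises to demonstrate safety and prove no additional or cumulative toxicity, which a 50-patient single-arm descriptive study cannot do: 0/50 events still leaves an upper limit of 7.1%

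*Protocol*

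**What the plan says.** Several sections announce a conclusion of safety:

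- Section 2 (Abstract, Purpose): "To demonstrate that thoracic epidural analgesia combined with intravenous lidocaine is safe and does not lead to adverse events during major abdominal surgeries".
- Section 3.2: from blood levels and an absence of events, "we hope to demonstrate no cumulative cardiac or neurological toxicity when both are used together".
- Section 3.4: treats safety as something the study will have demonstrated, and builds standardised practice and later superiority research on it.
- Section 3.5: "Proving that no additional adverse effects occur when these two techniques are combined" is the step that opens the way to comparative studies.
- Section 1 (Expected Outcomes): "It will affirm and provide evidence that combining intravenous lidocaine with epidural analgesia using ropivacaine in major open abdominal surgery is safe", with uniform adoption as the intended consequence.

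The operative sections describe something more modest. Section 6.1 states "This is a prospective, descriptive, single-center study" and section 10.4 confirms that "it is a single-arm descriptive study". The summary gives "SAMPLE SIZE: 50 patients". The objectives in 4.1 and 4.2 are to evaluate concentrations and to identify side effects. Section 12.1 sizes the study for the precision of one percentage. Section 12.2 plans two percentages, patients with any concentration outside the safe range and patients with a toxic event, each with a 95% confidence interval. No comparator, reference rate, acceptable upper limit or success criterion is stated.

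**The concern.** The announced conclusion and the design do not match, in three ways.

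1. *No additional* adverse effects and *no cumulative* toxicity are statements about a difference between the combination and each technique used alone. There is no such group. The clinical composite in 5.2 also includes bradycardia and tachycardia, which cannot be attributed to the combination without a control.
2. *Safe* has no numerical meaning in the protocol, because no rate is named above which the combination would be judged otherwise. The data therefore have no stated way to fail the claim.
3. Fifty patients cannot exclude uncommon events. The protocol itself calls the central nervous system effects rare (3.2) and cardiopulmonary arrest a rare event (Abstract).

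The stake is practical. The result is meant to support standardised and uniform use, so a reader could take an absence of events in 50 patients as proof of their absence in general.

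**Working it through.** **Inputs.** n = 50 (sections 1 and 12.1); one arm (10.4); 95% confidence intervals, asymptotic or exact (12.2), taken here as two-sided because the sidedness is not stated. The true event rates of 1%, 2% and 0.1% below are illustrative assumptions; the protocol names no rate of concern.

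**Step 1. The plan's own precision figures.** Asymptotic half-width = 1.96 × √(p(1−p)/n).

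- p = 0.10: 1.96 × √(0.10 × 0.90/50) = 0.083, or ±8.3% (width 16.6%).
- p = 0.50: 1.96 × √(0.50 × 0.50/50) = 0.139, or ±13.9%.

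The stated ±8% and ±14% are reproduced to the whole percent. They describe how precisely a percentage is estimated and do not define what would count as safe.

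**Step 2. The most favourable clinical result, 0 events in 50.**

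- Exact two-sided 95% upper limit: 1 − 0.025^(1/50) = 7.1%.
- Exact one-sided 95% upper limit: 1 − 0.05^(1/50) = 5.8%.
- Wilson two-sided upper limit: 7.1%. Rule of three: 3/50 = 6.0%.
- Simple asymptotic interval: half-width 1.96 × √(0 × 1/50) = 0, so it collapses to 0% to 0% and cannot be used here.

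If some patients are not evaluable (assumption), the exact two-sided limit rises to 7.9% with 45 patients and 8.8% with 40.

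**Step 3. Chance of seeing no event when the event exists.** P(0 events) = (1 − p)^50.

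| True rate | P(no event in 50) |
| --- | --- |
| 2% | 0.98^50 = 36% |
| 1% | 0.99^50 = 61% |
| 0.1% | 0.999^50 = 95% |

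For scale, zero events would put the upper limit at or below 1% only with ln(0.025)/ln(0.99), rounded up to 368 patients (two-sided), or ln(0.05)/ln(0.99), rounded up to 299 (one-sided).

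**Step 4. The comparative claims.** An additional effect is (rate under the combination) − (rate under one technique alone). The study observes only the first term. A larger n would narrow the interval for that term but give no information on the second, so no sample size repairs this part.

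**The case against.** The strongest reply is that the operative protocol is already descriptive. The objectives are to evaluate and to identify, the sample size rests on precision, there is no hypothesis test, and 12.2 already plans 95% confidence intervals. The strong wording sits in the Abstract and in the hypothesis and outcome prose. Section 3.2 only expresses a hope, and 3.4 and 3.5 present the study as a step towards comparative research. Much of this stands: no analysis, sample size or data collection is wrong on this ground. What does not stand is that the wording is therefore harmless. It is the stated purpose, it recurs in five places, and the summary ties it to adoption in practice.

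Three stronger readings may tempt a reader, and the document does not support them.

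- *That the primary endpoint hides dangerous joint exposure because each drug is judged against its own limit.* Suppose lidocaine 4.5 and ropivacaine 1.8 µg/mL at the paired 2 h sample. Section 3.3 gives a lidocaine half-life of 80 to 110 minutes. With simple exponential decline, the fraction left after 120 minutes is 2^(−120/80) = 0.354 to 2^(−120/110) = 0.470. A level of 4.5 then implies 4.5/0.470 = 9.6 to 4.5/0.354 = 12.7 µg/mL when the infusion stopped. The end-of-infusion sample would already have counted this patient as an event. The secondary composite also observes patients under the combination. A summed-fraction index would need an additivity assumption that the protocol does not supply.
- *That reducing concentrations to in or out of range discards the rest.* Section 12.2 also describes quantitative variables by mean, standard deviation, median and range.
- *That the plan expects 10% toxicity.* The 10% refers to levels outside the safe range, which for lidocaine includes values below 1.4 µg/mL. The upper bound of 6 µg/mL in 5.1 is well below the 15 µg/mL given there for neurotoxicity.

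**Conclusion.** The point holds as a mismatch between the announced conclusion and the design. Freedom from additional or cumulative toxicity cannot be estimated without a comparator, whatever the sample size. Absolute safety cannot be demonstrated without an acceptable upper limit. In the best case, 0/50, toxicity rates up to 7.1% (exact, two-sided 95%) or 5.8% (one-sided) remain compatible with the data, and a 1% event would be missed with probability 61%. These figures assume 50 evaluable, independent patients; fewer would raise the limits. The planned percentages and intervals remain valid estimates. The fault lies in what the protocol says they will prove, and it should be corrected because that conclusion is meant to guide practice.

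**What to change.** 1. In sections 1 (Expected Outcomes), 2 (Purpose), 3.2, 3.4 and 3.5, replace the claims of proof with the aim already set in 4.1 and 4.2. Suggested wording: to estimate the proportion of patients with concentrations above the stated limits, and the proportion with clinical toxicity, each with exact 95% confidence limits.
2. Remove the statements that safety will be demonstrated, that the absence of additional effects will be proved, and that cumulative toxicity will be shown to be absent. Leave those contrasts to the comparative studies that 3.4 and 3.5 foresee.
3. State that the safety conclusion rests on the exact upper confidence limit and not on the observed percentage or on an absence of events. For concentrations, base it on the above-limit count, because the outside-range percentage in 12.2 also includes low lidocaine values.

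The cost is an amendment of wording and a more modest claim. No change to the sample size, blood sampling or treatment follows from this point. Tolerance limits or a joint-exposure index are optional extras and are not needed to resolve it.
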